# Comparing a mindfulness- and CBT-based guided self-help Internet- and mobile-based intervention against a waiting list control condition as treatment for adults with frequent cannabis use: a randomized controlled trial of CANreduce 3.0

**DOI:** 10.1186/s12888-022-03802-9

**Published:** 2022-03-24

**Keywords:** Cannabis, Internet-based intervention, Self-help, Mindfulness, Cognitive-behavioral therapy, Randomized controlled trial

## Abstract

**Background:**

Though Internet- and mobile-based interventions (IMIs) and mindfulness-based interventions (generally delivered *in-situ*) appear effective for people with substance use disorders, IMIs incorporating mindfulness are largely missing, including those targeting frequent cannabis use.

**Methods:**

This paper details the protocol for a three-arm randomized controlled trial comparing a mindfulness-based self-help IMI (arm 1) and cognitive-behavioral therapy (CBT)-based self-help IMI (arm 2) versus being on a waiting list (arm 3) in their effectiveness reducing cannabis use in frequent cannabis users. Predictors of retention, adherence and treatment outcomes will be identified and similarities between the two active intervention arms explored. Both active interventions last six weeks and consist of eight modules designed to reduce cannabis use and common mental health symptoms. With a targeted sample size of *n* = 210 per treatment arm, data will be collected at baseline immediately before program use is initiated; at six weeks, immediately after program completion; and at three and six months post baseline assessment to assess the retention of any gains achieved during treatment.

The primary outcome will be number of days of cannabis use over the preceding 30 days. Secondary outcomes will include further measures of cannabis use and use of other substances, changes in mental health symptoms and mindfulness, client satisfaction, intervention retention and adherence, and adverse effects. Data analysis will follow ITT principles and primarily employ (generalized) linear mixed models.

**Discussion:**

This RCT will provide important insights into the effectiveness of an IMI integrating mindfulness to reduce cannabis use in frequent cannabis users.

**Trial registration:**

International Standard Randomized Controlled Trial Number Registry: ISRCTN14971662; date of registration: 09/09/2021.

## Background

The consumption of cannabis to a tetrahydrocannabinol (THC) level of 1% or greater is generally prohibited in Switzerland [1]. Nevertheless, it is – as in other countries [2, 3] – one of the most commonly used illicit substances, with about a third of individuals at least 15-years-old having used cannabis at least once [4]. Lifetime prevalence is highest among young adults (especially males), with more than half of 20–34-year-olds reporting they have used cannabis at least once [4]. In this age group, roughly 10% indicate that they have used cannabis within the previous 30 days, with almost 25% of these admitting (almost) daily use [4]. People who use cannabis have a one in five risk of developing a cannabis use disorder (CUD), and this risk increases if cannabis use is initiated early and it is used at least weekly [5]. People with a CUD are more likely to report symptoms of other mental disorders (e.g., mood disorders [6]) and frequent cannabis use is associated with negative physical and social consequences [7].

However, even people with CUD who perceive a need for treatment might be reluctant to seek traditional professional help. Reasons include their fear of stigmatization, a preference to rely on themselves, and financial and structural barriers [8, 9]. Self-help internet- and mobile-based interventions (IMI) help overcome these barriers. According to meta-analyses, Internet- and computer-based interventions seem to be effective at reducing cannabis use in the short-term, with small but significant effect sizes (ES) observed post-treatment [10, 11] and significant effects at 3-month [12] and 6-month [13], but not 12-month follow-up [10]. The studies that were included in the aforementioned meta-analyses predominantly used personalized feedback, motivational interviewing (MI) and/or cognitive-behavioral therapeutic (CBT) approaches.

CANreduce is also a self-help IMI for frequent cannabis users that draws on classical MI [14] and CBT approaches [15]. The program consists of eight modules that users can work through at their own pace over a period of six weeks. Two randomized three-armed controlled trials (RCT) have been conducted to test the effectiveness of versions of the program in existence at the time. Version 1.0 [16] was shown to be more effective reducing cannabis use when supplemented with the option of a brief professional chat (counseling) session, even though this option only was used by about one fifth of users. More precisely, small ES (0.20) were identified for the comparison between the study arm with chat counseling versus a waiting list control group at 3-month follow-up [17]. Hence, the chat invitation that was sent out by a health professional was possibly already sufficient to reduce participants’ cannabis use.

Based on this finding and following the theory behind the supportive-accountability model [18], it was hypothesized that a more automated eCoach would – similar to the health professional used in CANreduce 1.0 – increase both the program’s rate of adherence and effectiveness [19]. The eCoach who was incorporated in the first study arm of CANreduce 2.0 introduced the contents of most modules via a short video. Furthermore, weekly semiautomatic motivational and adherence-focused guidance-based feedback was sent out in her name, as were answers to any questions raised by users (in actuality, the questions were answered by anyone on the study team). The second study arm of CANreduce 2.0 only differed from the first arm by referring to an anonymous support team rather than to a personal eCoach (i.e., the same semiautomatic emails were sent to participants and all questions participants raised were answered in the same way), albeit without any videos. The second study arm, which had the anonymous support team, was found to be the most effective intervention, in terms of reducing cannabis use, with a moderate ES (d = 0.60) versus waiting list controls at 3-month follow-up [20]. Moreover, in this second study arm, CUD symptoms (measured using Cannabis Use Disorders Identification Test-Revised (CUDIT-R) [21], d = 0.52), cannabis dependence (Severity of Dependence Scale (SDS) [22], d = 0.60) and anxiety symptoms (d = 0.51) were reduced, this last reduction documented for the first time testing an IMI for cannabis users. That the ES for cannabis use reduction were much larger than in CANreduce 1.0 (see above) might also have been due to further adaptions that were implemented in both active study arms in CANreduce 2.0. Most importantly, frequently co-occurring mental health problems (e.g., symptoms of depression and anxiety, and sleep difficulties) among frequent cannabis users were addressed in CANreduce 2.0 via CBT-based approaches for depression and anxiety reduction and via social problem-solving skills training [23–25]. This adaptation was crucial, since comorbidities between frequent cannabis use and other mental disorders might dampen a treatment’s effectiveness [26]. Despite the larger ES observed with CANreduce 2.0, compared to both the previous version of the program and earlier digital interventions (ES = 0.11 [12]), there remains room for improvement.

One potential way to further improve the program would be to incorporate previously-neglected but promising approaches within IMI, including mindfulness. *Mindfulness* can be defined as the “awareness that emerges through paying attention on purpose, in the present moment and nonjudgmentally to the unfolding of experience moment by moment” [27]. Practicing mindfulness can be useful to people with substance use disorders (SUD), since their condition may be characterized by *mindlessness* [28] (i.e., habitual or stereotyped responses that may be carried out automatically without conscious volition or strategic consideration of the consequences that might arise from them [29]). Mindfulness has been suggested as a way to support people with SUD via various mechanisms [29, 30]; e.g., by helping them increase their awareness of triggers, habitual patterns, and ‘automatic’ reactions and by shifting their relationship to all internal and external experiences [31]. Mindfulness practices — like ‘mindful breathing’ — might help individuals to reorient their attention to the sensation of breathing when they are experiencing something distressing that typically would trigger them to use a particular substance [31]. There also is evidence that mindfulness techniques (e.g., mindful breathing) can evoke biological (e.g., altered brain activity) and subsequently behavioral mechanisms (e.g., decreased substance cue-reactivity) that may lead to improved clinical outcomes (e.g., decreased craving) [29].

Though some standardized mindfulness-based interventions (MBI) were not originally developed specifically for people with SUD (e.g., Mindfulness-Based Stress Reduction (MBSR; [32]), they are nevertheless sometimes applied to this target group [33]. Other interventions — like Mindfulness-Based Relapse Prevention (MBRP; [31]), Mindfulness Training for Smokers (MTS; [34–36]) and Mindfulness-Oriented Recovery Enhancement (MORE; [37]) — have been conceptualized specifically for people with a SUD. MBI – including those previously mentioned – are mostly conducted in an in situ group therapy format over several weeks (typically 8 weeks). During group sessions, clients are guided by a trained professional through various mindfulness practices that are subsequently debriefed in group processes that is typically followed-up by an introduction to new psychoeducational material [29]. They also are given homework, including mindfulness practices and assignments to self-monitor symptoms related to their SUD [29].

Several papers have addressed the question of whether the above-mentioned standardized and other MBI are effective treating people with SUD. In one systematic review and meta-analysis published by Li et al. [38], MBI were found to have a small effect reducing substance misuse, a medium effect reducing cravings, and a large effect reducing levels of stress relative to alternative treatments (e.g., treatment as usual (TAU), CBT, and a support group). Similarly, Cavicchioli et al. [39] detected small to large effects for MBI relative to other active programs for alcohol and drug use disorders (small effects for abstinence, levels of perceived stress, and avoidance coping strategies; moderate effects for symptoms of anxiety and depression; large effects for level of perceived craving, negative affectivity, and post-traumatic symptoms). Other meta-analyses and systematic reviews have also yielded promising results concerning the effectiveness of MBI treating SUD [33, 40–44]. One systematic review and meta-analysis that specifically focused on MBRP for SUD concluded that this MBI might – relative to other interventions – exert small effects on withdrawal/cravings and the negative consequences of substance use, but no effects on other outcomes (including relapse, frequency of use, symptoms of anxiety or depression) [45]. In summary, at least some published evidence exists that MBI might be helpful to people with SUD. Furthermore, MBI might be superior to other treatments for some subgroups with certain clinical (e.g., co-occurring SUD and depression [46, 47]) or sociodemographic characteristics (e.g. [48]).

Despite these promising findings, that most studies on the effectiveness of MBI hitherto focused on substances like tobacco, alcohol, or poly-substance use [33] must be considered. To the best of our knowledge, the effectiveness of MBIs treating frequent cannabis use has, to date, only been evaluated in two pilot studies. In the first, Dakwar and Levin [49] provided 10 weeks of weekly, individual mindfulness-based psychotherapy to 14 cannabis-dependent subjects. Of these, 11 completed the program (79%), and eight achieved abstinence (57% by intent-to-treat (ITT) analysis) by the end of treatment. In a second study, by de Dios et al. [50], the efficacy of a brief, two-sessions intervention that combined MI and mindfulness meditation was examined as a means to reduce cannabis use in young adult females. The intervention group consisted of 22 women, while an assessment-only control group numbered 12. Women randomized to the intervention group used cannabis on fewer days than controls one, two, and three months post treatment. Thus, even though these two pilot studies are limited by their small size, they nonetheless both suggest that MBI might also be feasible and effective for frequent cannabis users.

The need for larger, well-designed RCTs to study the effectiveness of MBI is not specific to frequent cannabis user, but other substance-related problems, as well [30]. Furthermore, Wilson et al. [30] have provided suggestions on how future research could address the implementation challenges of traditional MBIs. Among other things, these authors pointed out the lack of studies evaluating MBI delivered via technology-based platforms, even though this mode of delivery could expand such interventions’ reach [30].

Preliminary findings on web- and/or mobile-based MBI for SUD are promising [30]. However, to the best of our knowledge, no paper on the effectiveness or efficacy of mindfulness-based web self-help for frequent cannabis users has yet been published. This said, Hides et al. [51] have published their protocol for an RCT to determine the efficacy and cost-effectiveness of a web-based program that includes a small mindfulness component compared to an information-only control website among young cannabis users (16–25 years) with psychotic experiences (i.e., a narrow target group).

Based on the outlined research on the effectiveness and efficacy of web-based self-help interventions, as well as MBI, for people with SUD, and based upon existing research gaps (e.g., the lack of large RCTs and any web-based MBI for frequent cannabis users), the study presented in this protocol seeks to examine the effectiveness of a web self-help intervention (CANreduce 3.0) that incorporates mindfulness as a way to reduce cannabis use among adults, of any age, who use cannabis frequently.

## Study design and methods

### Design

The self-help IMI called *CANreduce 3.0* will be evaluated within a three-arm RCT, which will compare a mindfulness-based self-help IMI (arm 1); a CBT-based self-help IMI (arm 2); and a waiting-list control condition (arm 3) in their effectiveness reducing cannabis use among frequent cannabis users. Since the mindfulness-based self-help IMI (arm 1) contains newly-developed contents, testing its effectiveness is of primary interest in the current RCT. The CBT-based self-help IMI (arm 2) is a slightly-adapted version of CANreduce 2.0 [19] and serves as a reference program [52]. Performance of the reference intervention is, thus, not the main consideration; however, if the test (arm 1) and reference intervention (arm 2) both fail to demonstrate a statistically-significant advantage over the control condition, this could suggest that the trial is insensitive, or lacks assay sensitivity. If differences are observed, the difference between the reference intervention (arm 2) and controls can be used to help assess the practical relevance of the difference between arm 1 and the control condition [52].

Consistent with this, a confidence interval approach will be used as an exploratory tool to identify similarities between treatment arms 1 and 2 [53, 54]. The control condition (arm 3) will consist of all the same assessments administered to the other two subject groups (see Section Measures), as well as brief advice on the health risks of cannabis use (e.g., potential short-term and long-term effects). Some screening and brief internet interventions from Swiss addiction counselling also are available on the Internet and, as such, might be accessed by controls, but no links to them will be provided in CANreduce 3.0. Participants who are assigned to the control group will be offered the opportunity to receive the intervention delivered in study arm 1 after they complete the final assessment of the RCT, six months after they register for the study).

The trial has been registered with the ISRCTN registry (date of registration: 09/09/2021) and is traceable as ISRCTN14971662 (http://www.isrctn.com/ISRCTN14971662). It also has been approved by the Ethics Committee of the Faculty of Arts and Social Science at the University of Zurich, Switzerland (approval number: 20.4.17). Any important protocol modifications would be reported to this Ethics Committee.

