#### Study arm 2: CBT-based self-help IMI

The main changes to study arm 2 in CANreduce 3.0, relative to CANreduce 2.0, can be summarized as follows. First, a tutorial has been introduced that familiarizes participants with the features of the program (see above) to increase the program’s usability. These contents have already been described in Module 1. Secondly, the order of the modules has been changed, and the first four modules must be worked through one after the other before any of the remaining four modules can be started. In contrast, users of CANreduce 2.0 were permitted to work on the modules in whatever order they chose. These changes, as well as some slight changes in the wording of the modules’ titles, have been implemented so study arms 1 and 2 in the current CANreduce 3.0 study are similar (note that the sequential order of the first four modules in the mindfulness-based study arm is necessary, as the concepts introduced in modules 1–4 build upon each other). Thirdly, some minor language and content improvements have been implemented in each module (e.g., we changed the personal pronoun from the formal "you" (German "Sie") to the informal "you" (German "Du")). Fourthly, mindfulness-related content that existed in CANreduce 2.0 has been deleted to avoid any confounding effects between the two active study arms of the current study. Lastly, the eCoach was adapted. Even though the previous study on the effectiveness of CANreduce 2.0 revealed that the study arm having an anonymous support team (and not the personal eCoach who introduced the modules via a video) was the most effective, we still used an eCoach rather than an eTeam in this study arm of CANreduce 3.0. However, since it is possible that the eCoach in CANreduce 2.0 did not match all the participants’ expectations (e.g., in terms of gender or age), the eCoach for CANreduce 3.0 is now displayed schematically (as an avatar picture) and participants can choose between either a male or female version. Furthermore, and analogous to study arm 2, the eCoach now introduces each module in written form and summarizes the main lessons learned at the end of each module.

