### Hypotheses

The following detailed study hypotheses for the main outcome (i.e., reduction in the monthly days of cannabis use between baseline and the 3- and 6-month follow-up assessments) will be tested:A mindfulness-based self-help IMI for the reduction of cannabis use (study arm 1) is more effective than being on a waiting list (control condition, study arm 3).A CBT-based self-help IMI for the reduction of cannabis use (study arm 2) is more effective than being on a waiting list (control condition, study arm 3).A mindfulness-based self-help IMI for the reduction of cannabis use (study arm 1) is at least as effective as a CBT-based self-help IMI (study arm 2).

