### Data analyses

Data will be analyzed according to the ITT principle. Multiple imputation procedures, using the R package *mice* [87], will be used to address missing data. *mice* involves specifying a multivariate distribution for the missing data and drawing imputations from their conditional distributions by Markov chain Monte Carlo (MCMC) techniques. We intend to use 20 imputed data sets, as this has been deemed sufficient [87]. The imputation model will include all primary and secondary outcomes (see above). Adjunct variables, like sociodemographic data, will be included if they improve convergence within the imputation model.

Differences in primary and secondary continuous outcome variables between the two active study arms (1 and 2) at baseline and at both follow-up points will be tested using linear mixed models (LMM). The LMMs will be specified to model clusters and repeated measures by defining random effects for study condition and time (repeated measures). Appropriate distributions for non-normal continuous outcomes will be specified (e.g., negative binomial, zero-inflated). In addition to the ITT analyses, per-protocol analyses will be performed.

To investigate the exploratory research question of whether study arm 1 (mindfulness-based self-help IMI) results in a similar reduction in days of cannabis use as study arm 2 (CBT-based self-help IMI), a confidence interval approach will be used for the ES of the difference between these two study arms, using a two-sided 0.05 level of significance [54]. The equivalence margin is a priori set at d = 0.20, corresponding to the smallest value that would constitute a relevant effect [88]. The upper bound of the 95% CI for the ES will be compared against the predefined equivalence margin of d = 0.20 and must be below the margin to show equivalence.

Additional exploratory regression analyses will be conducted to determine whether baseline variables predict the frequency or quantity of cannabis use, severity of dependence (SDS), reduced psychiatric symptoms (PHQ-9, GAD-7), perceived stress (PSS-10) and mindfulness (MAAS) at 3 and/or 6 months follow-up, treatment retention, and adherence. For these analyses, we will use linear, multinomial, or binary regression models, depending on the scale used for the outcome measure. Treatment retention and client satisfaction will be compared between study arms one and two by Pearson chi-square analysis at week 6 (intervention end).

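### The rule for calling the mindfulness arm equivalent to the CBT arm is not tied to either arm beating the waiting list, so it can be met in the joint-failure case that the article itself calls insensitive

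*Protocol article*

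**What the plan says.** Three parts of the protocol article bear on this.

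- **Design.** Arm 2 is a reference programme whose own performance is not the main consideration. The article adds that "if the test (arm 1) and reference intervention (arm 2) both fail to demonstrate a statistically-significant advantage over the control condition", this could point to an insensitive trial. It then introduces the arm 1 versus arm 2 confidence interval as an exploratory tool. It attaches no consequence to joint failure.
- **Hypotheses.** Three hypotheses are listed for testing on "reduction in the monthly days of cannabis use between baseline and the 3- and 6-month follow-up assessments". The second is that "A CBT-based self-help IMI for the reduction of cannabis use (study arm 2) is more effective than being on a waiting list". The third is that arm 1 "is at least as effective as a CBT-based self-help IMI (study arm 2"). No order or dependence among them is stated.
- **Data analyses.** The arm 1 versus arm 2 question is again called exploratory. A confidence interval for the effect size is planned, "using a two-sided 0.05 level of significance". "The equivalence margin is a priori set at d = 0.20, corresponding to the smallest value that would constitute a relevant effect". Equivalence is shown if the upper 95% bound is below that margin. Arm 3 plays no part in the rule.

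**The concern.** A finding that a new programme matches a reference is informative only if the trial could have shown an effect. The article accepts this in Design and has the waiting-list arm needed to check it, but the decision rule does not use that arm. Read literally, the plan allows the conclusion that mindfulness is equivalent to CBT when both have failed against the waiting list.

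The efficacy of arm 2 also cannot simply be carried over from the earlier trial. The d = 0.60 in Background belongs to the CANreduce 2.0 arm with the anonymous support team. The section on study arm 2 says that this version "was the most effective, we still used an eCoach rather than an eTeam in this study arm of CANreduce 3.0". Existing mindfulness content was also deleted and the order of the first four modules fixed. Whether arm 2 works has to be shown in this trial.

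**Working it through.** **The plan's own figure.** The article gives no operating characteristics for arm 1 versus arm 2. Its one power figure, above 80% at 210 per arm, is for arm 1 versus arm 3. It cannot be rerun, because the intercept, random-effect variances, time coding and earlier sample size are not given. This point does not depend on it.

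**Inputs from the article.** 210 per arm (Power analysis); margin d = 0.20, two-sided 0.05, and a pass if the upper 95% bound is below 0.20 (Data analyses).

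**Assumptions.**
- A standardised difference at one follow-up point, with SE = sqrt(2/n) and no gain from covariates or repeated measures.
- Positive d means arm 1 is worse; the article does not define the sign.
- The Discussion expects relatively large drop-out but gives no figure. Losses of 30% and 50% are therefore assumed and treated as reduced effective n: 210 × 0.70 = 147 and 210 × 0.50 = 105.

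**Step 1: the rule as written.** P(pass) = Φ((0.20 − true d)/SE − 1.96). With a true difference of zero:

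| n per arm | SE | 95% half-width | Observed d must be below | P(pass) |
|---|---|---|---|---|
| 210 | 0.0976 | 0.191 | 0.009 | Φ(0.089) = 0.536 |
| 147 | 0.1166 | 0.229 | −0.029 | Φ(−0.245) = 0.403 |
| 105 | 0.1380 | 0.271 | −0.071 | Φ(−0.511) = 0.305 |

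Only the difference between arms 1 and 2 enters the formula. At 210 per arm, P(pass) is 0.536 whether both programmes have d = 0 or both have d = 0.60 against the waiting list.

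**Step 2: bring in the waiting list.** Three arm means were simulated (2,000,000 draws), with arms shared between contrasts so that the correlations are kept. An arm beats the waiting list if z > 1.96. At 210 per arm:

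| True effects against arm 3 | Rule as written | Pass and neither arm beats arm 3 | Pass, at least one arm beats arm 3 | Pass, arm 2 beats arm 3 |
|---|---|---|---|---|
| Both 0 | 0.536 | 0.513 | 0.023 | 0.003 |
| Both 0.20 | 0.536 | 0.165 | 0.370 | 0.205 |
| Both 0.30 | 0.536 | 0.028 | 0.508 | 0.424 |
| Both 0.60 | 0.536 | 0.000 | 0.536 | 0.536 |
| Arm 1 0.20, arm 2 0 | 0.984 | 0.449 | 0.535 | 0.021 |

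With two inert programmes, 0.513/0.536 = 96% of passes fall in the joint-failure case described in Design. Requiring at least one active arm to beat arm 3 gives 0.021 at 147 per arm and 0.019 at 105.

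**Step 3: an inert arm 1 beside a working reference.** If arm 2 has d = 0.20 and arm 1 has none, the true difference lies on the margin and P(pass) = Φ(−1.96) = 0.025. If arm 2 has the 0.11 that Background quotes for "earlier digital interventions (ES = 0.11 [12"]), then P(pass) = Φ((0.20 − 0.11)/0.0976 − 1.96) = Φ(−1.04) = 0.15.

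**The case against.** The strongest reply is that the safeguard is nearly in place. The assay-sensitivity warning comes directly before the paragraph introducing the similarity analysis. Both active-versus-waiting-list comparisons are planned, so a careful reader could discount an empty similarity result. The comparison is called exploratory in two sections, only arm 1 versus arm 3 was powered, and an analysis plan not shown here may add the condition. This lowers the weight of the point but does not remove it. The article fixes the margin, the bound and the conclusion, and Hypotheses lists the third hypothesis beside the other two without an exploratory label.

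A reader might also infer more than the documents support:

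- **That 0.54 is a false-positive rate.** It is the pass rate for any two equal arms. If both are inert, similarity is true in the literal sense; the harm lies in reading it as evidence that both work.
- **That joint failure is likely, or that the sponsor means to claim similarity after it.** The article says neither. It calls arm 2 a slightly adapted CANreduce 2.0. If arm 2 had d = 0.30, it would beat the waiting list with probability about 0.87 at 210 per arm.
- **That a noisier trial passes more easily.** The reverse holds: the pass rate falls from 0.54 to 0.30 as effective n falls from 210 to 105.
- **That the margin readily lets an inert arm 1 pass beside a working reference.** Step 3 gives 2.5% at d = 0.20 and 15% at d = 0.11, and hypothesis 1 already addresses that case.
- **That the claim must depend on arm 2 beating arm 3.** Design says reference performance is not the main consideration. Such a condition would bar the claim when arm 1 beats the waiting list and arm 2 narrowly misses, a case in which similarity does not mean that neither works.

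**Conclusion.** The point holds as a gap between the article's own assay-sensitivity criterion and its equivalence rule. Assay sensitivity was not overlooked; the recognised caveat was not connected to the decision. The rule can return equivalence when both active arms have failed against the waiting list, and taken alone it cannot distinguish two inert programmes from two equally effective ones. The size rests on the two-sample approximation and assumed losses above; the planned mixed model with multiple imputation would shift the probabilities, but the missing condition is a matter of text and does not depend on them. The consequence is confined to an exploratory claim, although one that readers are likely to quote.

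**What to change.** Add to Hypotheses and to Data analyses, in line with the joint-failure criterion in Design: *Equivalence, or the conclusion that arm 1 is at least as effective as arm 2, will be claimed only if at least one active arm is superior to arm 3 on the primary outcome. If both fail, the arm 1 versus arm 2 interval will be reported descriptively as uninterpretable for similarity. The arm 1 versus arm 3 and arm 2 versus arm 3 estimates will always be shown beside it.* As the main outcome is assessed at 3 and 6 months, state which follow-up the condition refers to.

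No new data are needed. The cost is some loss of claims when both programmes work equally but modestly, as the table in the working shows: it is small at d = 0.30, larger at d = 0.20, and nil at d = 0.60. Making the claim depend on arm 2 alone would cost more (0.42 rather than 0.51 at d = 0.30).
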